**Figure 3 figure3:**
[figure not shown]
Identifying differentially expressed genes (DEGs) and pathways activated by the treatment in objective 1 of the study protocol. IGF-1: insulin-like growth factor 1. LC-MS/MS: Liquid chromatography with tandem mass spectrometry; RNA-Seq: RNA sequencing.

The steps for the RNA-Seq include the following:

Total RNA will be extracted using a RNeasy extraction kit, with on-column DNase digestion.RNA quality will be assessed using an Agilent bioanalyzer.Samples will be analyzed on an Illumina HiSeq platform using standard protocols.For quantitative reverse transcriptase PCR validation of RNA-Seq results, a subset of the groups described in objective 1 will be used.The expression of identified differentially expressed genes will be compared in the publicly available RNA sequencing databases.

At the same time, we will use phosphoproteome analysis to identify differentially phosphorylated proteins between different study conditions using liquid chromatography with tandem mass spectrometry measurement.

The steps involved in the phosphoproteomics will be as outlined below:

Cell lysis, protein digestion, and labellingPeptide enrichment, immunoprecipitation, and offline fractionationMass spectrometry data acquisitionPeptide and protein database searchingProteomics data analysisPhosphoproteomics and acetyl-immunoprecipitation data analysis

### Objective 3: Bioinformatics

We will perform bioinformatics pathway analysis to identify any key genes and proteins involved in the association between PCOS and EC, after transcriptomic and phosphoproteomics profiling, as identified in objective 2 (Figure 4). The results from the same HEC-1-B and HEC-1-A cell lines and treatment groups, as outlined in objectives 1 and 2, will be used.

The methodology for the RNA-Seq data analysis will be as previously published [26], paired end raw reads (FASTQ format) will be quality- and adapter-filtered using Trim Galore wrapper for FastQC and Cutadapt [27]. The retained paired reads will be aligned to the Ensembl-annotated HG19 human Illumina iGenome build using Tophat2. Subsequently, differential gene expression will be calculated for the different cell culture study groups in comparison to the control specimen, using Cuffdiff, based on fold changes >1.5 and a *P* value <.05. Statistically significantly enriched gene ontologies and pathways for differentially expressed genes will be obtained using WebGestalt and the Cytoscape GeneMANIA plug-in. Next-generation RNA-Seq and associated clinical information will be obtained from publicly available data sets.

The methodology for the phosphoproteomics data analysis will also be as previously published data analysis for the phosphoproteomics data; label-free quantitative data will be filtered with a cutoff of ≥2 observations in the 4 repeats of at least 1 time point. Log transformation will be performed before any missing data points are imputed using random values generated from a normal distribution centered at the 1% quantile and the median SD. The abundance of phosphopeptides will be normalized to the abundance of corresponding parental proteins. The Limma package will be used in the R environment to identify differential proteins or phosphorylation with a false discovery rate–corrected ANOVA *P* value of .05. The k-means clustering approach will be used to analyze the patterns of the differential proteins and phosphorylation events. For functional annotation and network analysis, the differentially regulated proteins will be searched against the String database, and the networks will be visualized by using Cytoscape.

Although the study will aim to recruit 20 women with PCOS and 20 women without PCOS aged between 18 and 45 years, we will begin with a pilot study of samples from 3 women with PCOS and 2 controls and perform validation studies in the larger cohort of 20 women with PCOS and 20 women. The experimental plate design for the cell-culture studies in this feasibility study is illustrated in Table 1.

It will be 1 plate per cell line for each time point (24 h and 48 h). All experiments will be conducted in quadruplicates. We recognize that opinions differ about the ideal sample size for cell-culture experiments [28]; however, we believe our proposed experiments are stringent enough to make the results believable.

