**Methods:**

We intend to recruit 20 women with PCOS and 20 women without PCOS for this cross-sectional study. All experiments will be carried out 4 times to ensure consistency. We will perform transcriptomic and phosphoproteomic profiling to identify differentially expressed genes and phosphoproteins between different treatments using RNA sequencing and phosphoproteomics. We will also perform bioinformatics pathway analysis to identify whether any unique collection of genes or phosphoproteins explains increased EC risk in PCOS. The primary outcome measure will be the cell proliferation (growth) difference measured by cell index values. Our protocol stands out due to its unique approach; no previous study has used this approach to investigate the oncogenic effect of serum from women with PCOS. Additionally, no previous study has considered the differential mutations of genes related to the insulin signaling pathway across various types of human EC cell lines and the potential impact of these variations on their experimental findings.

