**Figure 4 figure4:**
[figure not shown]
Bioinformatics pathway analysis to identify any key genes and proteins involved in the association between polycystic ovary syndrome (PCOS) and endometrial cancer (EC).

**Table 1 table1:** Experimental plate design for cell culture studies.

Plates											
1	2	3	4	5	6	7	8	9	10	11	12
PCOS^a^ 1	PCOS 1 + IGF^b^	PCOS 1 + Inhibitor	PCOS 1 + IGF + Inhibitor	PCOS 2	PCOS 2 + IGF	PCOS 2 + Inhibitor	PCOS 2 + IGF + Inhibitor	PCOS 3	PCOS 3 + IGF	PCOS 3 + Inhibitor	PCOS 3 + IGF + Inhibitor
PCOS 1	PCOS 1 + IGF	PCOS 1 + Inhibitor	PCOS 1 + IGF + Inhibitor	PCOS 2	PCOS 2 + IGF	PCOS 2 + Inhibitor	PCOS 2 + IGF + Inhibitor	PCOS 3	PCOS 3 + IGF	PCOS 3 + Inhibitor	PCOS 3 + IGF + Inhibitor
PCOS 1	PCOS 1 + IGF	PCOS 1 + Inhibitor	PCOS 1 + IGF + Inhibitor	PCOS 2	PCOS 2 + IGF	PCOS 2 + Inhibitor	PCOS 2 + IGF + Inhibitor	PCOS 3	PCOS 3 + IGF	PCOS 3 + Inhibitor	PCOS 3 + IGF + Inhibitor
PCOS 1	PCOS 1 + IGF	PCOS 1 + Inhibitor	PCOS 1 + IGF + Inhibitor	PCOS 2	PCOS 2 + IGF	PCOS 2 + Inhibitor	PCOS 2 + IGF + Inhibitor	PCOS 3	PCOS 3 + IGF	PCOS 3 + Inhibitor	PCOS 3 + IGF + Inhibitor
Control 1	Control 1 + IGF	Control 1 + Inhibitor	Control 1 + IGF + Inhibitor	Control 2	Control 2 + IGF	Control 2 + Inhibitor	Control 2 + IGF + Inhibitor	Media (FBS^c^)	Media (FBS) + IGF	Media (FBS) + Inhibitor	Media (FBS) + IGF + Inhibitor
Control 1	Control 1 + IGF	Control 1 + Inhibitor	Control 1 + IGF + Inhibitor	Control 2	Control 2 + IGF	Control 2 + Inhibitor	Control 2 + IGF + Inhibitor	Media (FBS)	Media (FBS) + IGF	Media (FBS) + Inhibitor	Media (FBS) + IGF + Inhibitor
Control 1	Control 1 + IGF	Control 1 + Inhibitor	Control 1 + IGF + Inhibitor	Control 2	Control 2 + IGF	Control 2 + Inhibitor	Control 2 + IGF + Inhibitor	Media (FBS)	Media (FBS) + IGF	Media (FBS) + Inhibitor	Media (FBS) + IGF + Inhibitor
Control 1	Control 1 + IGF	Control 1 + Inhibitor	Control 1 + IGF + Inhibitor	Control 2	Control 2 + IGF	Control 2 + Inhibitor	Control 2 + IGF + Inhibitor	Media (FBS)	Media (FBS) + IGF	Media (FBS) + Inhibitor	Media (FBS) + IGF + Inhibitor

^a^PCOS: polycystic ovary syndrome.

^b^IGF: insulin-like growth.

^c^FBS: fetal bovine serum.

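### The planned RNA-Seq test has no term for the woman, so either PCOS-control P values are too small or same-serum treatment contrasts lose power, depending on a library unit the article does not state

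*Protocol article*

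**What the plan says.** The protocol article, Methods, Objective 3: Bioinformatics, names one test for RNA-Seq. Expression is compared "for the different cell culture study groups in comparison to the control specimen, using Cuffdiff, based on fold changes >1.5"; the second condition for calling a gene is significance at the .05 level. The section applies this to both cell lines and to the treatment groups of objectives 1 and 2. The sentence mentions no woman, no pairing and no combining of repeats, and it does not say which specimen is the control.

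On repeats, the same section says "All experiments will be conducted in quadruplicates", and the abstract gives the purpose: "All experiments will be carried out 4 times to ensure consistency". Table 1 shows each woman's serum alone, with IGF-1, with inhibitor and with both (for the first PCOS woman the last is "PCOS 1 + IGF + Inhibitor"), four wells each. A pilot of 3 PCOS women and 2 controls precedes the cohort of 20 and 20.

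For the phosphoproteins another tool is named ("The Limma package will be used in the R environment"), and there the .05 threshold applies after correction for the false discovery rate. The Results section says that data analysis had not begun.

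**The concern.** In Table 1 the repeats are nested in women and the treatments are crossed with women. A comparison of groups by label reflects neither feature.

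- **Nesting.** Four cultures of one serum share whatever is particular to that woman. If they enter as four replicates, the PCOS-control comparison claims more independent information than it has.
- **Crossing.** Serum with IGF-1 and the same serum alone come from the same woman. A test that ignores this leaves the variation between women in the error term of a contrast where it cancels.

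The gene list feeds the enrichment and network analysis, so objectives 2 and 3 both inherit the result. The IGF-1 and antagonist contrasts are also the ones closest to the study's stated aim, the role of IGF-1.

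**Working it through.** **Inputs from the article.** 4 repeats; 4 treatments per serum; 3 v 2 women, then 20 v 20; P <.05 and fold change >1.5. Table 1 is consistent: (3 + 2 + 1 medium) x 4 x 4 = 96 wells = 8 rows x 12 columns. The article gives no power, SD or correlation, so there is no figure of its own to reproduce.

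**Assumptions.** The share of variance between women (ICC) is 0.3, 0.5 or 0.8. Data are normal, and t tests stand in for Cuffdiff, so the sizes are illustrative.

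**(a) Each repeat is its own library: PCOS v control.** The variance of a group mean is understated by the factor 1 + (4 − 1) x ICC. For a large sample the true error is 2 x P(Z > 1.96/√factor).

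| ICC | Factor | 1.96/√factor | Formula | Simulated, 20 v 20 | Simulated, 3 v 2 |
|---|---|---|---|---|---|
| 0.3 | 1.9 | 1.42 | 0.155 | 0.155 | 0.169 |
| 0.5 | 2.5 | 1.24 | 0.215 | 0.219 | 0.250 |
| 0.8 | 3.4 | 1.06 | 0.288 | 0.293 | 0.367 |

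With one value per woman, the simulated error is about 0.05 in every row. At ICC 0 the repeats-as-independent test is valid.

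**Effect of the fold-change rule in (a).** A null gene must also show a mean log2 difference beyond log2(1.5) = 0.585. With S the total log2 SD between libraries, the SD of that difference is S x √{[ICC + (1 − ICC)/4] x (1/n₁ + 1/n₂)}. At ICC 0.5 this is S x √(0.625 x 0.1) = 0.25 S for 20 v 20, and S x √(0.625 x 0.833) = 0.72 S for 3 v 2. The joint false-call rate cannot exceed the smaller of P(|difference| > 0.585) and the type I error above.

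| S (assumed) | Upper bound, 20 v 20 | Upper bound, 3 v 2 |
|---|---|---|
| 0.3 | about 0 | 0.7% |
| 0.5 | below 0.01% | 10% |
| 0.75 | 0.2% | 25% |
| 1.0 | 1.9% | 25% |

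In the full cohort at ICC 0.8 and S = 1.0, the SD is √(0.85 x 0.1) = 0.29 and the bound is 4.5%.

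**(b) Repeats pooled to one value per woman: treatment contrast on the same sera.** Take 20 women, an effect of 0.5 SD and an assumed correlation of 0.7 between treatments.

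- Paired: the SD of the difference is √(2 x 0.3) = 0.775. The noncentrality is 0.5/0.775 x √20 = 2.89 on 19 df, with critical value 2.09. Power is 78%.
- Unpaired: the test uses a standard error of √(2/20) = 0.316, although the true one is 0.775/√20 = 0.173. A difference of about 2.02 x 0.316 = 0.64 is needed. Simulated power is about 25%.

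**Why (a) and (b) do not add.** If all repeats enter as separate libraries, an unpaired test of 80 v 80 values at library-level correlation 0.7 has simulated power of about 98%, not 25%. For such treatment contrasts the type I error with 20 women is 0.022 at ICC 0.3 and 0.008 at ICC 0.5, below nominal. That holds when the treatment effect does not vary between women. With woman-by-treatment variance of ICC/4, the error ranges from 0.04 to 0.11 over 3 or 20 women and ICC 0.1 to 0.8.

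**The case against.** The strongest reply is that the article never says each repeat becomes its own library. That is right. A reader might infer that four repeats are counted as four independent samples, because everything is done in quadruplicate, no pooling step is listed, and the phosphoprotein filter counts observations among the 4 repeats. It remains an inference, and pooling would remove (a) entirely. It would not restore the pairing in (b).

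Secondly, the fold-change rule limits the damage. In the full cohort it keeps the joint false-call rate below 5% at every setting shown, so a claim of hundreds or thousands of false genes there would need a rule the plan does not use. But this protection depends on a log2 SD that the article does not give, and in the pilot it is weak once S reaches 0.5. The pilot is, in fairness, called a feasibility study with validation to follow.

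Thirdly, the control specimen is singular and undefined, so a same-serum treatment contrast is not stated in so many words. This stands: (b) applies to any such contrast that is made.

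A reader might also infer that a planned false discovery rate correction fails. None is stated for RNA-Seq; the correction belongs to the phosphoproteins. Adding one would not repair (a): at ICC 0.5, Benjamini-Hochberg at 5% without the fold-change rule still passes about 61 (20 v 20) or 84 (3 v 2) of 1,000 null genes.

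Finally, the article condenses a fuller plan and refers to a published method, and that Cuffdiff accepts no blocking factor is general knowledge of the software. The point therefore rests on the comparison the article does state, which contains no woman term.

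**Conclusion.** The concern holds in conditional form. The stated RNA-Seq test does not fit the nested and crossed design of Table 1, and one of two errors follows.

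- With separate libraries, PCOS-control P values are too small: true type I error about 16%, 22% or 29% (20 v 20), or 17%, 25% or 37% (3 v 2), at assumed ICC 0.3, 0.5 or 0.8. The fold-change rule offsets this largely in the full cohort and much less in the pilot.
- With pooled libraries, those P values are sound, but a same-serum contrast has about 25% power where a paired test has 78%, at the assumed effect and correlation.

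It would be wrong to say that all the P values err in one direction, or to add the two harms at these sizes. RNA-Seq is secondary to the cell index outcome, but objectives 2 and 3 depend on it, so the change is worth making before analysis starts.

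**What to change.** Combine the four repeats for each woman x treatment x cell line x time point, and say whether this is done by pooling RNA or by summing counts. Replace Cuffdiff with a count model that accepts the woman as a block, for example limma-voom, since limma is already in the plan. Test PCOS v control between women, and IGF-1 and antagonist effects within woman. Name the control specimen for each contrast. This works under either reading of the library unit.

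The cost is a short change to the analysis text, different scripts and, if repeats would otherwise have been separate libraries, a shorter PCOS-control gene list. No new samples or sequencing are needed.

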### Objective 1: Comparing the Oncogenic Effect of PCOS Serum on EC Cell Lines With the Effect of Serum From Women Without PCOS (Controls) and IGF-1

To further investigate the possible role of IGF-1 in mediating the risk of EC in women with PCOS we will evaluate the proliferative effects of PCOS serum, IGF-1, and IGF-1 antagonists on human endometrial cancer 1-A and 1-B cell lines, through a comparison with controls (using serum from women without PCOS and cell culture media; Figure 2).

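### RNA-Seq genes are selected on P<.05 with fold change >1.5 and no named multiplicity adjustment, against an undefined control, and the list goes straight into pathway enrichment

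*Protocol article*

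**What the plan says.** All of the relevant text is in the protocol article, mostly under Methods, Objective 3: Bioinformatics.

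- **RNA-Seq rule.** Genes are selected "in comparison to the control specimen, using Cuffdiff, based on fold changes >1.5 and a *P* value <.05". No adjustment for the number of genes is named. The paragraph says that the method follows a cited publication.
- **Phosphoproteomics rule, next paragraph.** Limma is used to "identify differential proteins or phosphorylation with a false discovery rate–corrected ANOVA *P* value of .05".
- **Use of the RNA-Seq list.** "Statistically significantly enriched gene ontologies and pathways for differentially expressed genes will be obtained using WebGestalt and the Cytoscape GeneMANIA plug-in".
- **Comparator.** "differential gene expression will be calculated for the different cell culture study groups in comparison to the control specimen". That control is not defined. Under Objective 1, controls are of two kinds: "using serum from women without PCOS and cell culture media". Table 1 shows two control donors plus media, each alone, with IGF, with inhibitor, and with both.
- **Replication.** Experiments are run in quadruplicate. A pilot of 3 women with PCOS and 2 controls precedes the cohort of 20 and 20. The RNA-Seq text does not say whether the replicates are wells or women.
- **Later checks (Objective 2).** Quantitative RT-PCR is planned on a subset of the groups, and expression will be compared with public databases.

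**The concern.** A per-gene P<.05 applied across a transcriptome produces false calls in proportion to the number of genes tested. The fold-change filter removes some of them, but how many depends on the variance of each gene and on the replication. It fixes neither the expected number nor the share of false genes in the list.

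The authors apply an FDR correction to one omics layer and not to the other, so the two layers that are to be read together follow different error rules. The RNA-Seq list is the direct input to enrichment, and Objectives 2 and 3 depend on that step to name genes and pathways that might explain endometrial cancer risk in PCOS. Chance genes in the input can produce plausible pathways that do not replicate.

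The undefined control adds to this. The scientific question is PCOS serum against non-PCOS serum, and a reader cannot tell from the text that this is the contrast behind the gene lists.

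**Working it through.** The article gives no gene count, no variance and no expected number of false genes, so there is no figure of its own to reproduce.

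**Inputs from the article:** P<.05 and fold change >1.5, applied jointly; 4 replicates per condition; 20 and 20 women planned.

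**Assumptions (not in the article):** m = 12,000-20,000 tested genes; per-gene log2 SD of 0.2-0.7; two-sided test; independent genes; an ordinary two-sample t-test standing in for the Cuffdiff model.

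**Step 1, P<.05 alone.** Expected false genes = 0.05 × m. This gives 0.05 × 12,000 = 600 and 0.05 × 20,000 = 1,000. These are ceilings, because the plan also applies the fold-change filter.

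**Step 2, the joint rule.** For a gene with no true difference, the observed log2 difference d has standard error SD × √(2/n). The gene is called if the t-test gives P<.05 and |d| > log2(1.5) = 0.585. The probability of both was obtained by numerical integration over the distribution of the estimated variance, then multiplied by m:

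| n per group | log2 SD | P(false call) | m = 12,000 | m = 20,000 |
|---|---|---|---|---|
| 4 | 0.2 | 0.000035 | 0.4 | 0.7 |
| 4 | 0.3 | 0.0048 | 58 | 97 |
| 4 | 0.4 | 0.0214 | 257 | 428 |
| 4 | 0.5 | 0.0358 | 430 | 716 |
| 4 | 0.7 | 0.0469 | 563 | 939 |
| 20 | 0.3 | <0.00001 | 0 | 0 |
| 20 | 0.5 | 0.0002 | 3 | 4 |
| 20 | 0.7 | 0.0082 | 99 | 164 |

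Simulation of the same rule gives matching counts within sampling error.

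**Step 3, with FDR control.** In simulation, Benjamini-Hochberg at 5% plus the same fold-change filter (m = 15,000, n = 4) gave on average 0-0.2 false genes per comparison when nothing truly differs. It gave at most about 3 when 2-5% of genes truly change 2-fold. The stated rule with no true differences gave 0.6, 76, 532 and 706 at SD 0.2, 0.3, 0.5 and 0.7.

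**Step 4, share of the list.** With 2% of 15,000 genes (300) truly changed 2-fold, the stated rule gave these averages:

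- SD 0.2: 0.5 false and 299 true genes, 0.5/299.9 = 0.2% false.
- SD 0.3: 72 false and 288 true, 72/360 = 20%.
- SD 0.5: 528 false and 194 true, 528/722 = 73%.

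**Step 5, unit of replication.** Suppose four wells of one PCOS serum are tested against four wells of one control serum as if independent. Ordinary differences between two women are then called PCOS effects. With m = 15,000, a well SD and between-woman SD of 0.2 each give 0.064 × 15,000 = 960 such genes; 0.3 each give 0.201 × 15,000 = about 3,000. An FDR threshold does not remove these, because the P values themselves are too small.

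**The case against.** The strongest reply is that this is a discovery-stage threshold outside the primary outcome, in a condensed article that points to a published method. Quantitative RT-PCR, public databases and the larger cohort follow. Part of this stands. The primary outcome is not touched, the word unadjusted is an inference, and the cited method cannot be checked here. But the threshold is written out in the article itself, beside a paragraph that does specify FDR correction, so this is a stated rule and not a detail left elsewhere. RT-PCR covers a subset of groups and is not described as filtering the enrichment input. No different rule is stated for the larger cohort.

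Several stronger readings are tempting, and the article does not support them:

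- *The lists will contain hundreds of false genes.* Under the joint rule this needs a log2 SD of roughly 0.4 or more at 4 v 4. At 0.2 almost none remain.
- *The lists will be dominated by chance genes.* Step 4 shows that the false share can be anywhere from 0.2% to 73%, depending on a variance and a number of true effects that the article does not give.
- *Only one control specimen is used, and PCOS serum is never tested against control serum.* The wording is singular but undefined, and the aims describe the PCOS-versus-control comparison. What can be said is that the reference is not named.
- *There will be 44 gene lists* (11 groups × 2 cell lines × 2 time points). The article does not say that RNA-Seq is run at both times, or that all groups are tested against one control.

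**Conclusion.** The concern holds in a limited form. As written, the RNA-Seq rule does not control false discoveries, it differs from the authors' own rule for the phosphoproteomics, and its output goes directly into pathway enrichment. Each comparison may contain from almost no false genes to about 940 at 4 v 4, and from none to about 165 at 20 v 20. These ranges depend on the assumed gene count and variance, on independent genes and on a t-test in place of Cuffdiff. The qualitative conclusion does not: a fold-change cut is not an error-rate control, and the article names nothing else for RNA-Seq that is. The reference group and the unit of replication for the PCOS contrast are also left open, and both decide what a called gene means.

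**What to change.** In Objective 3, replace the plain P-value threshold with an FDR-adjusted one (q<.05, in line with the phosphoproteomics rule) and keep the fold-change filter. State that the reference for the PCOS question is control serum, that is, PCOS serum versus control serum, and that the woman, not the well, is the replicate. If the cited method already uses an adjusted value, say so in the text.

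The edit is two or three sentences, and the Results section says that data analysis has not begun. The real cost is shorter lists, and at 4 v 4 the loss can be large. In the simulation with 300 genes truly changed 2-fold, Benjamini-Hochberg with the filter retained on average 209 of them at SD 0.2, 11 at SD 0.3 and fewer than 1 at SD 0.5. The stated rule retained 299, 288 and 194. Changing the software or restricting enrichment to a few contrasts is a matter of preference and is not needed to correct this point.

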The primary outcome measure will be the difference in cell proliferation measured by cell index values during the xCELLigence real-time cell proliferation experiment. Comparison of cell index values from cells treated in different groups will be performed by the Kruskal-Wallis test followed by multiple comparison tests.

### Objective 2: Identifying Differentially Expressed Genes and Pathways Activated by the Treatment of Endometrial Cell Lines of the Different Study Groups Listed in Objective 1

We will perform transcriptomic profiling of endometrial cell lines to identify differentially expressed genes in response to different study conditions outlined previously, using RNA Sequencing (RNA-Seq) to identify the molecular targets and pathways involved in the oncogenic effects (Figure 3).

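### RNA-Seq genes are called at a plain P<.05 plus a fold-change cut, with no false discovery rate control, although the phosphoprotein analysis in the same section has it

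*Protocol article*

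**What the plan says.** Methods, Objective 3: Bioinformatics, sets the RNA-Seq rule. The comparison is worded as follows: "differential gene expression will be calculated for the different cell culture study groups in comparison to the control specimen". That control specimen is not defined further. The threshold for calling a gene is then given as "using Cuffdiff, based on fold changes >1.5 and a *P* value <.05", and neither an FDR nor a q value is mentioned. The genes go forward to enrichment analysis: "Statistically significantly enriched gene ontologies and pathways for differentially expressed genes will be obtained using WebGestalt". GeneMANIA is named as a second tool.

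The following paragraph of that section uses Limma to "identify differential proteins or phosphorylation with a false discovery rate–corrected ANOVA", with .05 as the threshold. FDR control is therefore named for one data type and not for the other.

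The steps listed under Objective 2 add a check ("For quantitative reverse transcriptase PCR validation of RNA-Seq results, a subset of the groups described in objective 1 will be used") and a comparison of the identified genes with public RNA-Seq databases. On scope, the article lists 12 treatment groups and says: "The results from the same HEC-1-B and HEC-1-A cell lines and treatment groups, as outlined in objectives 1 and 2, will be used".

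**The concern.** RNA-Seq tests a whole transcriptome. If each gene is tested at P<.05 without correction, about 5% of unchanged genes pass the P value filter in every contrast. The second filter, fold change above 1.5, removes such genes only when noise is low. When replicates vary a lot and are few, an unchanged gene that reaches P<.05 by chance will usually show a large apparent fold change too, so it passes both filters together.

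Objective 3 seeks its key genes and pathways for the link between PCOS and endometrial cancer in this list. If much of the list is chance, enrichment results and candidate genes can be chance as well. The later steps do not repair this: qPCR covers a subset of groups, and the enrichment test and the database comparison both take the list as input.

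**Working it through.** The article gives no false-positive count, power or variance for RNA-Seq, so there is no figure of its own to reproduce. The check asks how large the false share of the list can be under the stated rule.

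**From the article**
- Rule: P<.05 and fold change >1.5, taken here in either direction; log2(1.5) = 0.585.
- Replication: quadruplicate experiments (4 v 4), a pilot of 3 women with PCOS and 2 controls (3 v 2), and a full cohort of 20 and 20 (20 v 20, analysed by woman).

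**Assumed, not in the article**
- 12,000 genes tested.
- 200 to 1,000 of them truly changed 2-fold (log2 change of 1).
- Normal log2 expression with SD varied.
- A two-sample t test standing in for the Cuffdiff test.

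**P value filter alone**

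12,000 × 0.05 = 600 expected false calls per contrast if no gene is changed.

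**Both filters, by simulation**

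With k truly changed genes, a = the chance that an unchanged gene passes both filters, and w = the chance that a changed gene does:

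false share = a(12,000 − k) / [a(12,000 − k) + wk]

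Worked example, 4 v 4 at SD 0.5: 429 false calls among 12,000 unchanged genes gives a = 429/12,000 = 0.0358, and w = 0.65.
- k = 200: 0.0358 × 11,800 = 422 false and 0.65 × 200 = 130 true; 422/552 = 76%.
- k = 1,000: 0.0358 × 11,000 = 393 false and 0.65 × 1,000 = 650 true; 393/1,043 = 38%.

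| Comparison | log2 SD | False calls per 12,000 unchanged genes | w | False share (k = 1,000 to 200) |
|---|---|---|---|---|
| 4 v 4 | ≤0.2 | about 0 | about 100% | about 0% |
| 4 v 4 | 0.3 | 58 | 96% | 5-22% |
| 4 v 4 | 0.4 | 259 | 82% | 22-61% |
| 4 v 4 | 0.5 | 429 | 65% | 38-76% |
| 3 v 2 | 0.3 | 156 | 67% | 17-53% |
| 3 v 2 | 0.5 | 444 | 33% | 56-86% |
| 20 v 20 | ≤0.5 | 0 to 2 | about 100% | about 0-1% |
| 20 v 20 | 0.7 | 95 | 97% | 8-34% |

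Repeat runs move these shares by about one percentage point.

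**With FDR control**

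A separate simulation used 4 v 4, 10,000 genes and 500 truly changed 2-fold. It compared the stated rule with Benjamini-Hochberg at 5% plus the same fold-change filter.

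| log2 SD | List, stated rule | False share | List, with FDR | False share |
|---|---|---|---|---|
| 0.2 | about 500 | about 0% | about 447 | about 0% |
| 0.3 | about 525 | 9% | about 122 | about 1% |
| 0.4 | about 617 | 33% | about 4 | about 1% |

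FDR control keeps the error rate low, but at this size and moderate noise it leaves very little to report.

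**The case against.** Several counter-arguments have weight.

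- **The text never says unadjusted.** It says only P value and refers to a published method that is not available here, which might supply a corrected value. This stands as a caveat. But FDR is written out for phosphoproteins one paragraph later, so a reader will take the RNA-Seq P value as raw. If a q value is meant, the sentence still needs correcting.
- **The fold-change cut may be enough.** In Table 1 the replicates are repeat wells of one serum on one plate, so a low SD cannot be excluded, and at SD 0.2 or below the problem vanishes at 4 v 4. This also stands. The SD is not known in advance, however, and a filter that works only when noise is low does not control error.
- **The larger cohort validates the pilot.** At 20 v 20 analysed by woman, the stated rule is nearly clean up to SD 0.5. At SD 0.7 it is not, and the rule applies to the pilot as well.
- **This is discovery work.** True, and it bears on severity: the primary outcome is cell index, and participants are told that further studies must confirm any findings.

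Two stronger readings are tempting, and the article supports neither. A reader might infer that the RNA and phosphoprotein lists feed one network analysis, so that unequal error rates contaminate it. The article sends genes to WebGestalt and GeneMANIA and proteins to the String database, and describes no merged list. A reader might also multiply the false calls over 11 groups, 2 cell lines and 2 time points, that is 44 contrasts. The 24 h and 48 h times are given for the cell-culture plates and not separately for RNA-Seq, and the control specimen is undefined, so no grand total can be fixed.

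**Conclusion.** The point holds in a limited form. The article itself fixes a gene-calling rule without error control over the transcriptome, next to an analysis that has it. It does not follow that most of the list will be false. Under the stated assumptions the false share runs from about 0% (4 v 4 at log2 SD 0.2 or below; 20 v 20 up to SD 0.5, at most about 1%) to roughly three quarters or more (76% at 4 v 4 and 86% at 3 v 2, both at SD 0.5 with 200 true genes). The gene count, the number and size of true changes, the SD and the t test stand-in are all assumptions. Severity is should-fix: the candidate genes and pathways of Objective 3 are at risk, and the primary analysis is not.

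**What to change.** In the RNA-Seq paragraph of Objective 3, replace the plain P value threshold with a Benjamini-Hochberg FDR (q value) below .05, computed over all tested genes within each prespecified contrast and cell line. Name those contrasts and define the control specimen. Keep fold change above 1.5, in either direction, as a second filter. Send only the resulting list to WebGestalt, GeneMANIA, the choice of genes for qPCR and the public-data comparison.

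This takes a sentence or two and no new data, since q values come from the same P values. The Results section says that data analysis has not started, so the rule can still be set in advance.

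The real cost is sensitivity. At 3 v 2 or 4 v 4 the FDR list may hold few or no genes at SD 0.4 or more in the t test stand-in. If a raw-P list from the pilot is then wanted for planning, label it exploratory and do not report it as differentially expressed genes.
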